#### Analysis of quantitative data from students (Aim 3).

To explore the public-health impact of GlobalConsent in the two implementation-strategies groups, we will estimate comparative interrupted time-series (CITS) models for student-level primary outcomes (sexually violent behavior; prosocial intervening behavior) and student-level knowledge, attitudinal, affective, and capacity-related secondary outcomes (Table 6).

As a first step in the analysis, we will inspect pretreatment data closely to select the modeling approach that best fits the data. Given the multi-module nature of GlobalConsent and evidence from the efficacy trial [51], we expect to see immediate level changes (improvements) in all outcomes at the first post-test survey and slope changes for all outcomes, as cognitive, attitudinal, affective, and behavioral change attenuate *partially but not entirely* [51]. We expect to see greater immediate improvement and less attenuation in the HIS group than the LIS group. A basic CITS model for the frequency of men’s sexually violent behavior may take the following form: log(E(Y_ijt_)) = B_0_ + B_1_T_t_ + B_2_Z_j_ + B_3_P_t_ + B_4_T_t_*HIS_ij_ + B_5_P_t_*HIS_ij_ + v_ij_, where Y_t_ is the outcome for the i^th^ participant for the j^th^ university at time t, B_0_ is a constant term showing the average frequency of sexually violent behavior in the reference university before implementation; Z_j_ is a vector of university dummies to allow a separate intercept for each university; T_t_ is the time elapsed since study start, where t=1,…,10 quarters; B_1_ is the pre-implementation trend in the comparison (LIS) group, and Β_1_ + B_4_ is the pre-implementation trend in the HIS group; P_t_ is a vector of indicators for each post-implementation time period; B_3_ is the level change in the reference university in the post-implementation period; v_ij_ is the random effect for the i^th^ participant at university j which would allow random subject-to-subject variation in the intercepts at each university. The difference in the actual post-implementation performance from the projected post-implementation performance in the HIS group, less this same difference in the LIS group, is the estimate of HIS effects (B_5_). This formulation assumes that all universities in the HIS group share the same trend, and all universities in the LIS group share the same trend (though possibly different from the HIS trend). This assumption could be relaxed by modeling the trends as random effects. To assess whether the slope of performance changes after implementation, we may code P_t_ as a dichotomous variable that equals 0 in the pre-implementation period and 1 in the post-implementation period. The change in slope can then be estimated by adding a three-way interaction between the higher-intensity implementation indicator (HIS_ij_), post-implementation indicator (P_t_), and linear time trend (T_t_). In this formulation, P_t_ would be coded to be centered on the introduction of implementation, so B_5_ is interpreted as the immediate shift in outcomes following implementation. Inclusion of this interaction would allow implementation effects to grow or decline over time. A similar CITS model will be applied to investigate the impact of GlobalConsent on the incidents of men’s prosocial intervening behavior in the two implementation-strategies groups.

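### The optional slope-change version of the student model omits the P×T term and centres the period indicator instead of time; the base model is not affected

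*Protocol article*

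**What the plan says.** All the relevant text is in the protocol article, under Analysis of quantitative data from students (Aim 3).

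- Base model: "log(E(Y_ijt_)) = B_0_ + B_1_T_t_ + B_2_Z_j_ + B_3_P_t_ + B_4_T_t_*HIS_ij_ + B_5_P_t_*HIS_ij_ + v_ij". Here P is a set of indicators, one for each post-implementation period, and Z holds university intercepts. T "is the time elapsed since study start", in quarters.
- Slope version, indicator: "we may code P_t_ as a dichotomous variable that equals 0 in the pre-implementation period and 1 in the post-implementation period".
- Slope version, added term: "The change in slope can then be estimated by adding a three-way interaction between the higher-intensity implementation indicator". The two other factors named in that product are P and T. No P×T term appears in the equation or in the text.
- Reading of B5 in that version: "P_t_ would be coded to be centered on the introduction of implementation, so B_5_ is interpreted as the immediate shift in outcomes following implementation".
- Expected pattern: the section foresees "slope changes for all outcomes, as cognitive, attitudinal, affective, and behavioral change attenuate" partially, with less attenuation in HIS than in LIS. A slope change is therefore expected in LIS as well.

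**The concern.** In a comparative interrupted time series, the HIS effect on slope is the slope change in HIS minus the slope change in LIS. The model must therefore let the LIS slope change at implementation, and the P×T term does that. Without it, a slope change shared by both arms appears in the HIS coefficient.

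The second slip concerns where B5 is read. Once T multiplies P×HIS, B5 is the HIS–LIS difference at T = 0. Subtracting a constant from a 0/1 indicator does not move that point; only re-centring T does.

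Aim 3 expects outcomes in HIS to be both more favorable and more sustained. The slope version is the one offered to test directly whether effects grow or decline over time. If it were fitted as described, its slope coefficient and its immediate-shift coefficient would not carry the meanings the text gives them.

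**Working it through.** **Algebra of the slope version as written.** Let B6 be the coefficient of HIS×P×T.

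- LIS slope before implementation: B1. LIS slope after: B1. Its change is fixed at 0.
- HIS slope before: B1 + B4. HIS slope after: B1 + B4 + B6. Its change is B6.

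So B6 is the HIS arm's own slope change. If P×T is added with coefficient B7, the LIS change is B7 and the HIS change is B7 + B6, and B6 becomes HIS minus LIS.

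**Reading of B5.** With P×T in the model, the post-implementation HIS–LIS gap, net of the pre-implementation trends, is B5 + B6·T on the log scale. B5 is therefore the gap at T = 0, which is study start. Replacing P by P − 0.5 leaves both B5 and B6 unchanged; this was confirmed by refitting.

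**Inputs for a numerical illustration.**

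- From the protocol article: six universities, three per arm; three six-monthly surveys before delivery and three after; T from study start; a design incidence rate ratio (IRR) of 0.825, which reproduces as 0.65 + (1 − 0.65)/2.
- Assumed, because the documents do not give them: waves at T = 0, 2, 4, 6, 8, 10 quarters with delivery at T = 5; no pre-implementation trend; a common drop to 0.65; and attenuation rates of 0.02 to 0.05 log units per quarter.

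Poisson models were fitted to error-free expected values, so any departure from the truth comes from the specification alone.

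**Case A: identical arms (truth: B6 = 0, exp(B5) = 1.00).** Each cell gives the results for common attenuation of 0.02 / 0.03 / 0.05.

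| Slope model | HIS×P×T | exp(B5) |
|---|---|---|
| As written | 0.02 / 0.03 / 0.05 | 0.89 / 0.85 / 0.76 |
| T centred, no P×T | 0.02 / 0.03 / 0.05 | 0.99 / 0.98 / 0.98 |
| P×T added, T from study start | 0 / 0 / 0 | 1.00 / 1.00 / 1.00 |
| P×T added, T centred | 0 / 0 / 0 | 1.00 / 1.00 / 1.00 |

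**Case B: true immediate IRR 0.825, attenuation 0.05 in LIS and 0.02 in HIS.** The true slope difference is 0.02 − 0.05 = −0.03.

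- Without P×T, HIS×P×T is +0.02, the HIS arm's own change. The sign is wrong: HIS looks less sustained when it is more sustained.
- With P×T but T from study start, HIS×P×T is correct at −0.03. However, B5 = log(0.825) − (−0.03)(5) = log(0.825) + 0.15, so exp(B5) = 0.825 × 1.162 = 0.96.
- With slope differences of −0.02 and +0.02 instead, the same formula gives 0.825 × e^0.10 = 0.91 and 0.825 × e^−0.10 = 0.75.
- With P×T added and T centred, the fit returns 0.825 and −0.03 exactly.

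**Base model on the same cases.** With one indicator per post-implementation period, the HIS ratios at the three post waves are 1.00, 1.00, 1.00 in Case A. In Case B they are 0.801, 0.754, 0.710, which equal the true 0.825 × e^(−0.03×1), e^(−0.03×3) and e^(−0.03×5).

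**False-positive rate of HIS×P×T.** This was simulated with identical arms, 1,719 men per arm, student-level heterogeneity and assumed baseline rates of 0.2, 0.5 and 1.0 acts per wave. Without P×T the rates were 0.09, 0.20 and 0.34 at attenuation 0.02, and 0.41, 0.74 and 0.97 at attenuation 0.05. With P×T they stayed between about 0.03 and 0.07.

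**The case against.** Four points count on the other side.

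- **The extension is optional.** The article says P may be coded this way, and the base model itself is offered as a form the analysis may take. The base model absorbs shared attenuation and answers the question of sustained effects wave by wave. This stands, and it limits the scope of the point.
- **An analyst might fit P×T anyway.** Adding a three-way interaction often implies its lower-order terms, and the text does not say that P×T is excluded. This stands in part. The equation is written out term by term without P×T and the text names only the three-way term, so following the document does not lead to the right model.
- **Centring P may be a slip for centring T.** The intent, that B5 be the immediate shift, is plain from "would be coded to be centered on the introduction of implementation". If it is read that way, the bias in B5 in Case A falls to about 1–2%. The slope coefficient remains wrong as long as P×T is missing.
- **The model form is not locked.** The article plans to inspect pre-treatment data and to vary the impact model in sensitivity analyses. This makes sole reliance on the slope version unlikely but does not correct its stated interpretation.

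**Conclusion.** The concern holds for the optional slope-change version and for that version only. As written, its HIS×P×T coefficient is not the HIS–LIS difference in slope change, and its B5 is not the immediate shift. The first error matters because the protocol itself expects attenuation in LIS; if LIS had no slope change, HIS×P×T would be unbiased. The second matters, even with P×T included, whenever the arms' slope changes differ.

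The sizes rest on assumed attenuation rates and on delivery midway between the third and fourth surveys. The error in the slope coefficient equals the LIS slope change, whatever that is.

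Three stronger readings are tempting but not supported:

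- That the Aim 3 comparison as a whole is wrong. The base model is sound on this point.
- That the trial would report a spurious immediate benefit close to its design IRR of 0.825. The 0.85 figure needs both slips taken literally: with identical arms, centring T gives 0.98 and adding P×T gives 1.00.
- That the cost-effectiveness ratio is contaminated. Aim 4 uses the actual-minus-projected contrast, which the article defines with the base model and does not tie to the slope version.

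This should be fixed; it does not invalidate the planned primary comparison.

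**What to change.** Rewrite the slope-change sentences so that T, not P, is centred at the start of GlobalConsent delivery, P is 0/1, and the model contains T, P, T×HIS, P×HIS, P×T and HIS×P×T together with the university intercepts and the random intercept. State that HIS×P×T is the HIS–LIS difference in slope change and that P×HIS is the immediate shift. Make the same change where the model is applied to prosocial intervening behavior.

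The cost is a few lines of text, one more parameter and slightly wider intervals. No change to data collection or to the base model is needed.

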
#### Power for analyses of student data (Aim 3).

We estimated the power to test models that tested for differences in the frequency of sexually violent behavior and prosocial intervening behavior between LIS and HIS groups. Using estimates for the mean frequency of sexually violent acts in the GlobalConsent Trial [51], we computed the statistical power with a generalized linear mixed model with a random intercept for repeated count measures via a simulation. We used the Stata command (ipdpower, model 2, a simulations-based command that calculates power for mixed-effects modeling with random effects for intercept) to perform the simulation. With a retained sample size of ~3,439 men (4,776 X 0.80 participation X 0.90 retention the final wave; ~1,719 in each implementation group), six counts for the frequency of sexually violent acts, an incidence rate ratio of 0.825 (0.65+(1–0.65)/2) for the rate of change after implementation of GlobalConsent for the HIS group relative to the LIS group, alpha level of .05, and 5000 simulations, estimated power was .91.

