## Assignment of interventions: allocation

### Sequence generation {16a}

All universities in the sample are broadly matched on programs of study (health sciences) and are pair-matched on region (North, Central, South). Within matched pairs, universities will be randomized using a computer random number generator to receive ‘lower intensity’ (LIS) or ‘higher intensity’ (HIS) implementation strategies to deliver GlobalConsent to eligible undergraduate men.

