#### Statistical power for analyses of faculty data (Aim 2).

We estimated the power to test the DD models that tested for differences in the knowledge of sexual violence legality and harm between LIS and HIS groups. Using estimates for the mean score measuring the knowledge of sexual violence legality and harm in the GlobalConsent Trial [50, 51], we computed the statistical power with a linear regression model allowing a separate intercept for each university via a simulation. We used the Stata command (ipdpower, model 1, a simulations-based command that calculates power for simple linear regression modeling) to perform the simulation. With a retained sample size of ~2,543 faculty (3,532 X 0.80 participation X 0.90 retention at wave three; ~1,272 in each implementation group), a point estimate of δ of 0.12, alpha level of .05, and 5000 simulations, estimated power was .85.

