##### University faculty analysis.

DD methods provide unbiased effect estimates if the trend over time would have been the same between the treatment (HIS) and comparison (LIS) groups in the absence of the more intense elements of HIS implementation. However, selection bias may arise if the composition of these groups changes over time, such that the faculty population at participating universities changes systematically, for example, through substantial turnover or consolidation. One approach to address this issue is to restrict the sample of faculty to those who are available across all three survey waves and study years (1, 3, 5). If high turnover risks a substantial loss of power using this approach, we will consider the use of propensity score weighting to handle this type of confounding across four groups (HIS pre, HIS post, LIS pre, LIS post) [85] Another challenge in this analysis is the cluster-randomized design, where six universities are assigned to HIS or LIS groups. We will assess the robustness of our DD findings across a range of small-sample corrections, and we will report the methods used and findings to ensure transparency and reproducibility [86, 87].

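### The student power of .91 and the basic CITS test of B5 assume no university-to-university variation in change and student-level inference, although only six universities in three pairs are randomised

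*Protocol article*

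**What the plan says.** **Randomisation.** Sequence generation {16a} pairs the six universities by region and then states: "Within matched pairs, universities will be randomized using a computer random number generator". That gives three universities per arm.

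**Student power (Power for analyses of student data, Aim 3).** The sample is counted in students: "With a retained sample size of ~3,439 men (4,776 X 0.80 participation X 0.90 retention the final wave; ~1,719 in each implementation group"). There are six counts per man, an incidence rate ratio of 0.825, alpha .05 and 5000 simulations, and the result is .91. The method is described as follows: "we computed the statistical power with a generalized linear mixed model with a random intercept for repeated count measures via a simulation". No between-university variance, intraclass correlation or design effect is stated.

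**Student model (Analysis of quantitative data from students, Aim 3).** The basic CITS model has a dummy for each university and one random effect, for the student, "which would allow random subject-to-subject variation in the intercepts at each university". The section states openly that all universities within an arm are taken to share one trend, and adds: "This assumption could be relaxed by modeling the trends as random effects".

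**Faculty, by comparison.** The University faculty analysis paragraph says: "Another challenge in this analysis is the cluster-randomized design, where six universities are assigned to HIS or LIS groups". It then commits: "We will assess the robustness of our DD findings across a range of small-sample corrections". The faculty power of .85 was nevertheless computed with "a linear regression model allowing a separate intercept for each university via a simulation". The matching list for male students covers an offset, seasonality and time-varying confounders, over-dispersion, autocorrelation, alternative model forms and reporting bias. It mentions neither clustering by university nor the small number of clusters.

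**The concern.** B5 contrasts the pre-to-post change in the HIS universities with that in the LIS universities. University dummies and student intercepts take out differences that are constant over time. They leave untouched any tendency for one university's change to differ from another's in the same arm. With three universities per arm, that variation cannot be separated from the effect of the strategies except by comparing universities with one another. A model that sets it to zero judges B5 against student-level noise alone.

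Two things are at stake. The first is the stated power for the two primary behavioural outcomes, which describes an analysis with thousands of independent units rather than six. The second is the false-positive rate of that test if universities do differ in their change. The same double difference is also the net-effectiveness term of the incremental cost-effectiveness ratio, so understated uncertainty could carry into Aim 4.

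**Working it through.** **1. Reproducing the plan's inputs**
- Retained students: 4,776 × 0.80 × 0.90 = 3,438.7, which agrees with 3,439.
- Effect: 0.65 + 0.35/2 = 0.825, and ln 0.825 = −0.1924.
- Power .91: this cannot be confirmed or refuted exactly, because the baseline mean count and the intercept variance are not given. It is attainable as a student-level figure. A Poisson calculation with the Table 1 enrolments × 0.72 reaches .91 at about 0.24 acts per wave without trend terms, or about 1.05 with the T and T × HIS terms. It is not an arithmetic error.

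**2. Precision implied by .91** (two-sided alpha .05 assumed, since sidedness is not stated)

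SE(B5) = 0.1924 / (1.960 + 1.341) = 0.1924 / 3.301 = 0.0583.

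**3. Adding between-university variation in change**

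Let tau be the SD, between universities in the same arm, of the log pre-to-post change. The protocol gives no value, so tau is an assumption shown over a range. A tau of 0.10 means that universities differ in their change by about 10% (one SD).

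- Total SE = √(0.0583² + tau² × (1/3 + 1/3)).
- Type I error of the student-level test = 2 × [1 − Φ(1.960 × 0.0583 / total SE)].
- Power with universities as units: noncentral t with noncentrality 0.1924 / total SE. Degrees of freedom are 4 for an unpaired three-versus-three comparison (critical value 2.776) or 2 for three pairs (critical value 4.303). The paired column assumes that pairing does not reduce tau.

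| tau (assumed) | Total SE | Type I error, student-level test | Power, 4 df | Power, 2 df |
|---|---|---|---|---|
| 0 | 0.0583 | 5.0% | .70 | .44 |
| 0.05 | 0.0712 | 10.8% | .54 | .33 |
| 0.10 | 0.1003 | 25.5% | .31 | .21 |
| 0.15 | 0.1356 | 40.0% | .20 | .14 |
| 0.20 | 0.1734 | 51.0% | .14 | .11 |

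**4. Check by simulation** (Table 1 sizes × 0.72, six waves, 1,500 runs per setting, with and without trend terms)
- Student-level test, no effect: rejection .05 at tau 0, .12 at 0.05, .28 to .29 at 0.10, .54 to .55 at 0.20.
- University-level tests, no effect: rejection stayed near .05 throughout.
- Power at tau 0: .90 to .92 for the student-level test, .65 to .66 on 4 df and .40 to .42 on 2 df. Unequal university sizes explain why the last two fall slightly below the formula.

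**5. Faculty figure**

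Power .85 at δ = 0.12 implies SE = 0.12 / (1.960 + 1.036) = 0.12 / 2.996 = 0.040. With universities as units and tau = 0, power is .62 (4 df) or .39 (2 df).

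**The case against.** The strongest reply is that the model is not final. The team will first inspect the pretreatment data to choose the modelling approach, the CITS equation is offered as a basic form that may be used, the shared-trend assumption is disclosed, and random trends are named as a relaxation. The variance structure and degrees of freedom could properly be settled in an analysis plan that is not shown. The student list also considers time-varying confounders, including concurrent training programmes and COVID-related changes at the universities, which are plausible sources of university-by-period variation.

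This softens the point about the model but does not remove it. The random-trend option is not committed to, concerns trends only and comes with no small-sample degrees of freedom. Covariate adjustment does not replace inference at the level of the six randomised units. The .91 is a fixed, published number, and its description contains none of these refinements. The faculty paragraph shows that the issue was recognised elsewhere in the same document.

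A reader might infer more than the documents support:
- **That the B5 p-value is certainly anti-conservative.** This needs tau above zero. The protocol gives no tau, and at tau = 0 the type I error is nominal.
- **That any p < .05 would rest on the student-level model alone.** Three pairs give 2³ = 8 allocations, so an exact randomisation test cannot give a two-sided p below 2/8 = .25. But the protocol plans no such test, and a university-level t-test can fall below .05 under a normality assumption.
- **That the faculty analysis ignores clustering.** It does not, since small-sample corrections are planned. What remains open there is mainly the .85.

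**Conclusion.** The point holds in conditional form. The .91 is a power given no university-to-university variation in change within an arm and large-sample, student-level inference. The power loss does not depend on tau: the small number of randomised units alone takes .91 to about .70 or .44, according to whether the pairing is broken or kept. Any positive tau lowers it further.

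Inflation of the type I error does depend on tau. It is absent at zero and is about 11%, 25% and 40% at assumed values of 0.05, 0.10 and 0.15. The documents do not show which value is realistic. These figures also rest on the SE implied by .91, a two-sided test and equal weight for each university. As the protocol stands, the student section states a power that its randomised design does not support without those unstated conditions, and it lacks the small-cluster provision given to faculty.

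**What to change.** - Make the primary Aim 3 inference respect the randomised unit. Either analyse each university's adjusted log pre-to-post change, or add a university-by-period random effect with small-sample degrees of freedom.
- State in advance whether the regional pairing is kept (2 df) or broken (4 df).
- Extend to students the small-sample corrections now planned for faculty.
- Replace .91 with power over a stated range of tau, and restate the faculty .85 in the same way.
- Report the HIS–LIS contrast as an estimate with its interval rather than leaning on a significance test.

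The cost is revised analysis wording and a re-run of the simulations. Intervals will be wider and the stated power less favourable. No universities or students are added, and data collection does not change.
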